#### Statistical methods for primary outcome

The primary endpoint of this study is a composite of time to death from any cause or respiratory insufficiency (DRI; defined as tracheostomy or the use of non-invasive ventilation for ≥22 h per day for ≥10 consecutive days). For each individual we will calculate the primary endpoint as [date of event/censor – date of randomization]/365.25. An indicator variable will be defined specifying whether the patient was alive or had an event at the end of the study. To test the difference between treatment arms, we will use a likelihood ratio test stratified for the randomization factor “*trial site*” and adjusted for “*TRICALS Risk Profile*” as continuous variable. The TRICALS Risk Profile will be fitted as linear effect. This likelihood ratio test will also be used for sequential monitoring of efficacy during one pre-specified interim analysis. The Kaplan-Meier plots estimating the cumulative event rate will be provided for each treatment group. In case of non-proportional hazards, we will estimate the mean difference in Restricted Mean Survival Time (RMST).

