#### Secondary outcomes

Combined effect on daily functioning and overall survival based on a joint model of survival and ALSFRS-R total scores.Daily functioning, defined as mean change from baseline in ALSFRS-R total score. Disease progression will be monitored using the ALSFRS-R, which is a validated 12-item questionnaire designed to evaluate the functioning of respiratory, bulbar, fine and gross motor function in ALS patients [22]. The total score ranges from 48 (no limitation in daily activities) to 0 (total inability). The ALSFRS-R slope, the difference in scores standardized for time, is often used as measure of disease progression in clinical trials and is significantly associated with survival [23].Respiratory function, defined as mean change from baseline in Slow Vital Capacity (SVC). The SVC is associated with survival in ALS patients [24]. The obtained estimates of the vital capacity will be recorded in liters and standardized using the GLI-2012 reference standard [25].Change in outcome of Plasma creatinine. Plasma creatinine is a part of the safety tests and will be used as one of the secondary endpoints to monitor disease progression [26]. Plasma creatinine is well correlated with functional decline, muscle strength and is highly predictive for overall survival. Due to the effect of disease progression on plasma creatinine, Cystatin C will be used for monitoring kidney function as safety parameter [27].Clinical disease stage, defined as mean time spent in each stage of the King’s and ALS Milano-Torino staging systems. The King’s staging system is a simple clinical staging system, which defines four stages of ALS. The first three stages are defined by functional involvement of a region: bulbar, upper limbs and lower limbs. The number of regions involved gives the stage. Stage 4 is reached if swallowing (4A) or respiratory (4B) difficulty is severe enough to require intervention. This procedure takes the form of a semi-structured interview. MITOS is a similar clinical staging system, in which the stages are defined as loss of independence on the four domains of the ALSFRS-R: swallowing, walking/self-care, communicating and breathing [28]. Studies have shown that both King’s staging and the ALS-MITOS correlate with survival [29, 30].Safety based on the safety assessments including neurological examinations, clinical laboratory evaluations, vital signs and frequency of adverse events (AEs) or serious adverse events (SAEs). (S)AEs will be categorized according to the Common Terminology Criteria for Adverse Events and will be rated for severity and association with study drug.Tolerability defined as time-to-discontinuation of assigned treatment since randomization.Change from baseline in urinary P75^ECD^. P75 is a neutrotrophin receptor that is expressed after motor neural damage and excreted through the urine [31]. Hence, presence of P75^ECD^ in the urine is indicative for the degeneration of motor neurons. P75^ECD^ has been shown to increase over time in patients with ALS and correlates well with measures of functional decline. Moreover, the marker is associated as independent predictor of survival. Therefore, P75^ECD^ may have the utility as a potential pharmacodynamic biomarker and slowing of a rising urine level may be indicative of a biological effect.Change from baseline in plasma Neurofilament light and heavy chain. Neurofilament light and heavy chains in ALS are well known to be correlated with prognosis and remain relatively stable over time [32]. A change in the expression of neurofilament light and/or heavy chain may, therefore, be considered as supporting evidence of disease amelioration in ALS.Neuropsychological status, defined as change from baseline on the ECAS and ALS-FTD-Q. Approximately 35% of the patients, with ALS, experience cognitive or behavioral impairment. The cognitive and behavioral impairment may increase as disease progresses [33]. The neuropsychological status of patients will be evaluated using the Edinburgh Cognitive and Behavioral ALS Screen (ECAS) [34]. The ECAS is independent of motor disability and evaluates five cognitive domains: language functions, executive functions, and letter fluency, memory and visuospatial functioning. If available, ECAS version A and B will be alternated to prevent a training effect in patients. The questionnaire has a behavior screen with a carer interview, this part will not be performed in this study. In addition, we will evaluate behavioral disturbances using the ALS frontotemporal dementia questionnaire (ALS-FTD-Q) [35]. The ALS-FTD-Q is a validated instrument for the screening of behavioral disturbances in ALS. The ALS-FTD-Q has 25 items (including three cognitive items: memory, concentration, and orientation in time), with a 4-point rating scale; the maximum score is 100. A higher score indicates more behavioral disturbances.Global quality of life (QoL), defined as change from baseline on the visual analog scale (single-item scale) and EQ-5D. QoL will be measured using a visual analog scale (single-item scale): a horizontal line of 100 mm ranging from 0 (worst imaginable QoL) to 100 (perfect QoL) [36]. Generic QoL will be measured using the EQ-5D. The EQ-5D measures the health status in terms of five dimensions: mobility, self-care, usual activities, pain and depression. From the EQ-5D a quality-adjust life year (QALY) can be calculated, which is required for cost-utility analysis if a drug is beneficial for patients with ALS [37]. If a patient deceases during the follow-up period, the date will be recorded. If a patient reaches the criteria for respiratory insufficiency (tracheostomy or the use of non-invasive ventilation for ≥22 h per day for ≥10 consecutive days), the date this criterion was met will be recorded and the patient will no longer be part of the study. The time point for all secondary outcomes is month 24.

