## Data collection and management

### Plans for assessment and collection of outcomes {18a}

During each clinical assessment patients will be asked about their current medication use and potential (serious) adverse events. All prescription drugs, over-the-counter medications, nutraceuticals, and herbal remedies will be recorded in the electronic case report form (eCRF). Additionally, ALS specific interventions such as gastrostomy placement, recommendation for wheelchair- and non-invasive ventilation (NIV) use will be recorded. Basic vital signs measurements (systolic and diastolic blood pressure, respiratory rate, heart rate and temperature) and body weight will be obtained. Details of all pregnancies in female patients and, female partners of male patients will be collected after the start of study drug and until conclusion of the pregnancy.

The ALSFRS-R questionnaire, the King’s- and ALS-MITOS staging will be filled out. Lung function is evaluated by using a non-invasive spirometer of the brand EasyOne to determine the Slow Vital Capacity (SVC), of which the highest of three attempts will be registered. During each follow-up period a venipuncture will be performed; approximately 20 ml will be obtained (4 tubes). All safety assessment will be evaluated locally. At baseline, Beta – HCG will be determined for female study patients. Additionally, patients will be asked to provide a urine sample. The urine sample (20 ml) will be used to screen for safety (dipstick or other method) and pregnancy.

Patients can optionally partake in lumbar punctures and CMAP scans. During the lumbar puncture, one vial (approximately 5 mL) of cerebrospinal fluid will be obtained at baseline, month 6 and month 12. Blood (serum and plasma), urine and CSF collected for biomarkers will be stored locally at −80 °C for at least the duration of the trial. CMAP scans will be made at baseline and months 3, 6, 9, and 12.

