#### Demography and baseline characteristics

Continuous variables are expressed as mean and standard deviation for normally distributed variables and median and range for non-normally distributed variables. Categorical variables will be presented as number of cases and percentage. Baseline characteristics will be compared between the placebo and intervention arm without significance testing. Demography will be summarized by allocation arm (active *vs.* placebo) and overall. Missing data will not be imputed unless otherwise specified. The following baseline variables will be calculated:Body mass index = weight (kg)/height^2^ (m)SVC _Predicted_ (L) = Predicted using GLI equation (Age, height, ethnicity, sex)Predicted %SVC = [SVC _Observed_ (L)/SVC _Predicted GLI2012_ (L)]*100% [48]Diagnostic delay (months) = [date diagnosis – date symptom onset]/365.25Symptom duration (months) = [date randomization – date symptom onset]/365.25ΔFRS = [ALSFRS-R _Baseline_ – 48]/symptom duration [49]TRICALS risk category: quintiles of the linear predictor based on the model described in Westeneng et al. [19]. Linear predictor is based on age, diagnostic delay, %SVC _Baseline_, ΔFRS, FTD, site of symptom onset, and El Escorial classification (see also {10} Eligibility criteria).Utrecht stage: Based on the ENCALS model, the median survival time from onset is predicted per patient (in months). Utrecht Stage is defined as symptom duration/median predicted survival time. Staging categories are I = 0–0.25; II = 0.25–0.5; III = 0.5–0.75; and IV = >0.75.

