### Methods for additional analyses (e.g., subgroup analyses) {20b}

Subgroup analyses for the primary endpoint will be carried out separately for two predefined subgroups in the same manner as described in the relevant section.

These subgroups are:Utrecht stage: early vs. late (<0.25 vs. >0.25).Neurofilament light chain: high vs. low.

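### Adding baseline neurofilament light to the primary model would be a cheap gain in efficiency; the present model is defensible and not an error

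*Protocol article*

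**What the plan says.** All references are to the protocol article.

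- **Statistical methods for primary outcome.** Treatment is compared by a "likelihood ratio test stratified for the randomization factor" trial site, with the TRICALS Risk Profile as a continuous covariate: "The TRICALS Risk Profile will be fitted as linear effect". No other covariate is named. The interim uses the same test: "This likelihood ratio test will also be used for sequential monitoring of efficacy during one pre-specified interim analysis".
- **Demography and baseline characteristics.** The score's inputs are listed: "Linear predictor is based on age, diagnostic delay, %SVC", followed by ΔFRS, FTD, site of onset and El Escorial class. Neurofilament is not among them.
- **Secondary outcomes.** One outcome is "Change from baseline in plasma Neurofilament light and heavy chain". On its meaning, the protocol says "Neurofilament light and heavy chains in ALS are well known to be correlated with prognosis and remain relatively stable over time".
- **Methods for additional analyses {20b}.** One of the two predefined subgroup factors for the primary endpoint is "Neurofilament light chain: high vs. low".
- **Participant timeline (Table 1) and Plans for assessment and collection of outcomes {18a}.** Blood is drawn at baseline, and samples "collected for biomarkers will be stored locally at −80 °C for at least the duration of the trial". No assay date is given.
- **Sequence generation {16a}.** Randomisation is stratified by site and TRICALS risk category, not by neurofilament.

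**The concern.** In a proportional hazards model, leaving out a covariate that predicts outcome pulls the estimated treatment hazard ratio towards 1 and lowers power, even when randomisation has balanced the covariate. Here a covariate that the protocol itself links to prognosis will be measured at baseline and joined to the primary endpoint for a subgroup analysis, but the primary model does not use it.

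The trial is small: 72 events, 57 patients on placebo and 80% planned power. A few points of power from data already collected would be worth having. A chance imbalance in neurofilament would also go uncorrected, except through whatever neurofilament shares with the TRICALS score.

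**Working it through.** **1. The plan's own figure.** Inputs from Sample size {14}: hazard ratio 0.50, one-sided 0.025, 80% power, 2:1 allocation.

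- Events (Schoenfeld) = (1.960 + 0.842)² / [(2/3)(1/3)(ln 0.50)²] = 7.849 / (0.2222 × 0.4805) = 73.5, so 74 against the stated 72.
- Power at 72 events = Φ(√(72 × 2/9) × 0.693 − 1.960) = Φ(0.813) = 79.2%.
- With the Table 2 bounds (0.36 and 2.60 at 41 of 72 events, 1.99 at the end, futility bound obeyed), power is 78.2%.

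The stated design reproduces within two events and two points of power.

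**2. Effect of omitting neurofilament.** The check is a simulation of the site-stratified Cox likelihood ratio test.

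- From the protocol: 171 patients, 2:1, 14 sites (Study setting), accrual over 31 months (171 / 5.5 per month), at most 24 months of follow-up, analysis at the 72nd event.
- Assumed, because the documents give no figure: TRICALS hazard ratio 1.65 per SD, median time to event 16 months, neurofilament independent of TRICALS, a range for the neurofilament hazard ratio per SD given TRICALS, and a true treatment hazard ratio of 0.50 given both covariates.
- Single look, critical value 1.96, 2000 trials per row.

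| Neurofilament HR per SD | Power, TRICALS only | Power, with neurofilament | Gain (points) | Median estimated HR, without / with |
|---|---|---|---|---|
| 1.00 | 76.3% | 76.8% | 0.5 | 0.499 / 0.495 |
| 1.22 | 75.4% | 76.5% | 1.1 | 0.499 / 0.493 |
| 1.49 | 72.2% | 75.4% | 3.2 | 0.513 / 0.496 |
| 1.82 | 66.8% | 73.5% | 6.7 | 0.530 / 0.495 |

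Simulation error is about 1 point per power figure, so the first row shows no difference. One-sided type I error was 2.5 to 2.8% with or without the covariate. Both models start below 80% because dividing 72 events among 14 strata costs information. The comparison between columns is the result that matters.

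**3. Missing baseline values.** If 10% of patients have no value and are dropped, power with neurofilament is 72.2, 71.7, 70.0 and 69.3% down the rows. That is below the TRICALS-only test in the first three. Mean value plus missing indicator avoids this. Two further site-stratified simulations used the final bound 1.99, 10% missing at random, and a neurofilament-TRICALS correlation of 0.3 (3000 trials per setting) or 0.4 (1000 trials per setting). Power is given as without / with complete data / with 10% missing and indicator:

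| Neurofilament HR per SD | Correlation 0.3 | Correlation 0.4 |
|---|---|---|
| 1.00 | 75.8 / 75.8 / 75.8% | 73 / 73 / 73% |
| 1.22 | 74.9 / 75.6 / 75.6% | 72 / 73 / 72% |
| 1.49 (1.5 in the second run) | 71.2 / 74.5 / 74.0% | 70 / 74 / 72% |
| 1.82 | 66.8 / 72.5 / 71.7% | 64 / 69 / 68% |

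Type I error in the 0.3 run was 2.2 to 2.4%.

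**4. Interim on the present model, final on the extended one.** With the same model at both looks, the two statistics correlate at about √(41/72) = 0.755 and the efficacy bounds give a one-sided error of 0.0251. With different models the correlation changes somewhat. Whatever it is, the error cannot exceed P(Z > 2.60) + P(Z > 1.99) = 0.0047 + 0.0233 = 0.0280.

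**The case against.** The strongest reply is that nothing is wrong. The model is fixed in advance, stratified by site, and adjusted for a composite of seven prognostic factors from a cross-validated survival model built on 11,475 patients. Adding a covariate is then a preference. This stands: the section contains neither an error nor a contradiction.

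Second, correlation with prognosis is not information beyond TRICALS. The Discussion supplies a caution of its own: UNC13A homozygosity shortens median survival by about six months, yet was not an independent predictor in the ENCALS model, because clinical characteristics carry the effect. This also stands, and is why the assumed range begins at 1.0.

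Third, the protocol does not define the hazard ratio of 0.50 as conditional on neurofilament. It is a conservative value set against a crude 0.43 and an adjusted 0.30. If 0.50 is the effect in the planned model, the design loses nothing and neurofilament could only add to its power. That is fair; the figures compare two models and do not show a shortfall against the design.

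Fourth, missing samples could undo the gain. This holds if patients are dropped, but not under the indicator rule.

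A reader might infer that power is certainly being thrown away, or that the loss reaches double figures. An unstratified simulation with a neurofilament hazard ratio of 2.0 per SD does give 65% against 78%, but the trial's test is stratified by site. The documents also give no figure for neurofilament beyond TRICALS, so neither inference is supported. Nor is this the only lever on power, since stratifying 72 events by site has its own cost.

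**Conclusion.** The point holds as an optional gain in efficiency. Omitting baseline neurofilament light costs about 0 to 7 points of power in the site-stratified test when its hazard ratio per SD beyond TRICALS lies between 1.0 and 1.8. The gain is 0 to about 6 points if the two are correlated at 0.3 to 0.4, and 0 to about 5 points with 10% missing and the indicator rule. The treatment hazard ratio is estimated at about 0.53 instead of 0.50 at the top of the range and is practically unchanged at the bottom. Including a covariate that adds nothing has no measurable cost.

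These sizes rest on assumed prognostic strengths and event rates, a linear neurofilament effect, values missing at random, and a single look at 72 events. The direction follows from the model; the size for this trial cannot be known from the protocol.

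**What to change.** Before any unblinded look, specify that:

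- the primary model at the final analysis adds log baseline plasma neurofilament light as a continuous covariate, alongside the site strata and the TRICALS profile;
- a patient without a baseline value receives the mean, with a missing indicator in the model, so that all randomised patients remain in the analysis (the rule must be written down, because the baseline section allows no imputation unless specified);
- the present model is reported as the sensitivity analysis;
- the interim uses either the present model or the extended one with an early assay of the baseline samples.

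The wording is cheap and needs no extra patients, visits or samples. The real cost is logistic: baseline samples stored at the sites must be assayed before the final analysis, or before the 41-event interim if the extended model is used there. If the present model is kept for the interim, the plan should acknowledge that the two looks use different models. If assay timing cannot be assured, the extended model can serve as a pre-specified sensitivity analysis instead, giving up the power gain in the primary test.

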#### Statistical methods for secondary outcomes

ICombined assessment of daily functioning and survival, defined as death from any cause [50, 51]. A joint model will be constructed between a survival model and a longitudinal model for ALSFRS-R data to evaluate the combined effect on both endpoints simultaneously; the full testing procedure is described elsewhere [52]. In short, the survival sub-model will contain treatment allocation as covariate and will be stratified for randomization factors “trial site and adjusted for “TRICALS Risk Profile” as a continuous variable, where the baseline hazard function follows a Weibull distribution [53]. A mixed effects sub-model will be fitted for the ALSFRS-R data with a random intercept and random slope for time per individual. The fixed effects part contains: baseline ALSFRS-R, treatment, time, baseline ALSFRS-R*time and treatment*time. Time will be fitted both linearly as well as non-linearly using restricted cubic splines. The non-linear effect of time will be kept in the model only if significant. If not, fixed non-linear time will be deleted first, followed by random non-linear time. An unstructured covariance matrix will be used to model the correlations among repeated measures. A likelihood ratio test will be used to compare a joint model with the treatment terms vs. a joint model without the treatment terms, thereby estimating the combined effect on both the ALSFRS-R and mortality, irrespective of their association.IIALSFRS-R scores will be analyzed using the same joint model framework outlined above to account for the informative censoring due to patient death (i.e., mortality-adjusted progression). Here, we will use a likelihood ratio test to evaluate the time*treatment interaction from the ALSFRS-R sub-model. A similar strategy will be applied for change from baseline in Predicted %SVC, plasma creatinine, and QoL.

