### Eligibility criteria {10}

A patient must meet all of the following criteria to be eligible to participate in this study:Age ≥ 18 years at the time of screening.Diagnosis of ALS according to the revised El Escorial criteria (possible, probable- laboratory supported, probable or definite) [16].Capable of providing informed consent and complying with trial procedures, including randomization to sub-studies.TRICALS risk profile > -6.0 and < −2.0**.The use of riluzole will be permitted during the study. Patients taking riluzole must be on a stable dose for at least 30 days prior to the baseline visit or stopped taking riluzole at least 30 days prior to the baseline visit.Women of childbearing potential, i.e., following menarche and until becoming post-menopausal unless permanently sterile, must have a negative pregnancy test at baseline and be non-lactating.Men must agree to practice contraception for the duration of the trial and for at least 3 months after last dose of study drug.Men must not plan to father a child or to provide sperm for donation for the duration of the trial and 3 months after the last dose of study drug.Women must not be able to become pregnant (e.g., post-menopausal (i.e., no menses for 12 months without an alternative medical cause), surgically sterile or using effective birth control methods) for the duration of the study. Effective contraceptives are defined as having a failure rate of less than 1% per year when used consistently and correctly and, when applicable, in accordance with the product label, including: abstinence, hormonal contraception, intrauterine device in place for ≥ 3 months.

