** The TRICALS risk profile is estimated using an open-access calculator, and is based on seven clinical disease characteristics [17]. The TRICALS risk profile can be conceptualized as a relative summary of prognostic information and is a predictor of the disease progression rate during follow-up [18]. The risk profile indicates how patients compare to each other (i.e., who is faster or slower progressing than average) without estimating the absolute survival time or probability. It is based on the ENCALS survival model, a cross-validated model to predict the composite endpoint death or respiratory insufficiency based on data of 11,475 patients with ALS [19]. The eligibility window was determined using clinical trial data from six independent trial cohorts comprising 1028 patients with ALS [18]. We searched for the optimal eligibility window that resulted in the most homogenous trial population in terms of ALSFRS-R progression without exceeding an exclusion rate of 25.0%.

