## Assignment of interventions: allocation

### Sequence generation {16a}

Randomization will be done using a centralized online response system (Research Online, Utrecht, the Netherlands, and Castor EDC, Amsterdam, The Netherlands), which assigns each randomized participant a unique identification number which will be used throughout the study. Randomization sequences in the study will be in random block sizes of 3–9, and stratified for trial site and risk category (high vs. low risk; low risk defined as a TRICALS risk profile of ≤ −4.5).

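### The ALSFRS-R sub-model leaves out the TRICALS risk profile and its interaction with time, so the treatment-by-time confidence interval is likely wider than it needs to be

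*Protocol article*

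**What the plan says.** In the protocol article, Statistical methods for secondary outcomes, item I describes a joint model of survival and ALSFRS-R. The survival half is stratified by trial site and adjusted for the TRICALS risk profile as a continuous covariate. For the longitudinal half: "A mixed effects sub-model will be fitted for the ALSFRS-R data with a random intercept and random slope for time per individual". Its mean structure is then listed: "The fixed effects part contains: baseline ALSFRS-R, treatment, time, baseline ALSFRS-R*time and treatment*time". Item II tests the time-by-treatment term from this sub-model and applies a similar approach to predicted %SVC, plasma creatinine and quality of life. Efficacy: other study parameters refers back to item II for urinary P75 and neurofilament.

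Elsewhere the article says of the profile:

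- Eligibility criteria {10} makes it an inclusion criterion ("TRICALS risk profile > -6.0 and < −2.0"), and the note to that section says it "is a predictor of the disease progression rate during follow-up".
- Sequence generation {16a} has randomisation "stratified for trial site and risk category", with the category cut at −4.5.
- Statistical methods for primary outcome adjusts for it: "The TRICALS Risk Profile will be fitted as linear effect".
- Demography and baseline characteristics gives its inputs: "Linear predictor is based on age, diagnostic delay, %SVC _Baseline_, ΔFRS, FTD, site of symptom onset, and El Escorial classification".

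General methods classes all secondary endpoints as exploratory, reported with 95% confidence intervals.

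**The concern.** The two halves of one joint model are adjusted differently, and the article gives no reason. The half without the profile is the one that estimates rate of decline, which is what the article says the profile predicts.

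Variation in slope that a known baseline value could explain stays in the random-slope variance, and that variance drives the standard error of treatment by time. Ignoring a prognostic factor used to balance the arms also means the analysis takes no credit for that balance, which makes the standard error conservative.

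At stake is the width of the interval for the ALSFRS-R slope difference and the power of the likelihood ratio tests in items I and II. The primary endpoint, its 72 events and the interim boundaries are not affected.

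**Working it through.** **Plan's own figure.** None exists for this point. The article states no power, slope variance or residual variance for ALSFRS-R. The 72 events belong to the primary endpoint and are not an input here.

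**Where the profile is used**

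| Use | Profile included? |
|---|---|
| Eligibility | yes, so known for every eligible patient |
| Randomisation | yes, as two categories |
| Primary analysis | yes, continuous and linear |
| Survival half of the joint model | yes, continuous |
| ALSFRS-R half of the joint model | no |

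Baseline ALSFRS-R by time, which is in the model, is not a full substitute. Among the listed inputs of the profile, the baseline ALSFRS-R score enters only through ΔFRS, where it is combined with symptom duration. Age, diagnostic delay, %SVC, FTD, site of onset and El Escorial class are separate inputs.

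**Ceiling on the gain.** Let R² be the share of between-patient slope variance that the profile explains beyond baseline ALSFRS-R. If that variance were the only source of error, the standard error (SE) would be multiplied by √(1 − R²).

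- R² = 0.01: √0.99 = 0.995, a fall of 0.5%
- R² = 0.04: √0.96 = 0.980, a fall of 2.0%
- R² = 0.10: √0.90 = 0.949, a fall of 5.1%
- R² = 0.25: √0.75 = 0.866, a fall of 13.4%

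**With residual error.** In a random-intercept, random-slope model with complete visits,

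SE² = (1/114 + 1/57) × [σ_b²(1 − R²) + σ_e²/S],

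where S is the sum of squared deviations of the post-baseline visit times from their mean. The arm sizes and quarterly visits are from the article. Visits at months 3 to 24 give S = 378, and months 3 to 12 give S = 45. The variances are assumptions: residual SD σ_e = 2 points, slope SD σ_b = 0.4 or 0.6 points per month. Hence σ_e²/S = 4/378 = 0.0106 or 4/45 = 0.0889.

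Example with 24 months, σ_b = 0.6 and R² = 0.25:

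- without the profile: 0.36 + 0.0106 = 0.3706, SE = √(0.02632 × 0.3706) = 0.0988
- with it: 0.27 + 0.0106 = 0.2806, SE = √(0.02632 × 0.2806) = 0.0859
- fall: 1 − 0.0859/0.0988 = 13%

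| Fall in SE | R² = 0.01 | 0.04 | 0.10 | 0.25 |
|---|---|---|---|---|
| Ceiling | 0.5% | 2.0% | 5.1% | 13.4% |
| 24 months, σ_b = 0.6 | 0.5% | 2.0% | 5.0% | 13.0% |
| 12 months, σ_b = 0.6 | 0.4% | 1.6% | 4.1% | 10.6% |
| 12 months, σ_b = 0.4 | 0.3% | 1.3% | 3.3% | 8.4% |

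**Bias.** Randomisation balances the profile in expectation, so leaving it out should not shift the estimate materially. A small simulation of the mixed model with risk-dependent death agreed. With and without the profile terms, the mean estimates were 0.261 and 0.260 at R² = 0.10, and 0.208 and 0.201 at R² = 0.30. The SE ratios (with over without) were 0.97 and 0.88. At 12 runs per setting this is only a plausibility check.

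**The case against.** **The planned model is not wrong.** It already adjusts for baseline ALSFRS-R and its effect on slope, and a standard error wider than necessary errs on the safe side. The endpoints are exploratory. All of this stands, and it sets the weight of the point.

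**The gain may be small.** The article gives no correlation between the profile and the slope. The eligibility window was chosen for homogeneous ALSFRS-R progression, which narrows the profile's range, and ΔFRS overlaps with the baseline score already fitted. Follow-up may also be short: under Interim analyses {21b}, in the futile scenario only 11.3% of patients remain for 18 months or more. This stands too, and is why the assumed range of R² starts at 1%.

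**The stratification argument is modest.** Two risk categories across 14 or 15 sites make 28 to 30 strata. With 171 patients that is about six per stratum (171/28 = 6.1; 171/30 = 5.7), against blocks of 3 to 9. Many blocks may stay incomplete, so little balance may be forced. Trial site, the other stratification factor, is also missing from the list.

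**The text is a summary.** The article abbreviates and refers to a cited source for the full testing procedure. But the fixed effects are set out as a definite list, so this is something the article fixes rather than leaves open.

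A reader might infer more than the document supports:

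- **That the slope estimate is biased or the test invalid.** Randomisation protects the comparison; only precision is affected.
- **That the change is worth a fixed number of extra patients.** That would need slope and residual variances and an R², none of which the document gives.
- **That every outcome modelled in a similar way would gain.** The article links the profile to rate of disease progression. It does not say that the profile predicts slopes of quality of life, P75 or neurofilament. Secondary outcomes describes neurofilament levels as fairly stable over time, which leaves little slope to explain.

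**Conclusion.** The point holds as a minor loss of precision in an exploratory analysis. By the article's own account the profile is prognostic for the rate being modelled, is available for every eligible patient, and is adjusted for in the other half of the same model. Leaving it out likely makes the treatment-by-time interval for ALSFRS-R wider than it needs to be.

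The size is not known. Under the assumption that the profile explains 1% to 25% of between-patient slope variance beyond baseline ALSFRS-R, the standard error would fall by at most about 0.5% to 13%. With 12 months of visits and the assumed slope SD of 0.4, the same range gives about 0.3% to 8%. The confident part is the omission and its direction; the magnitude rests wholly on assumed variances. The primary conclusion of the trial does not depend on it.

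**What to change.** Add the continuous TRICALS risk profile and its interaction with time to the fixed effects of the ALSFRS-R sub-model, alongside the existing baseline ALSFRS-R terms. Put both in the model with treatment terms and in the model without them, so that each likelihood ratio test still isolates treatment. State this before unblinding, since a covariate added later would look data-driven.

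The same terms can be carried into the parallel models for consistency with the stratified design. No precision gain should be claimed there for creatinine, quality of life, P75 or neurofilament.

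The cost is two model terms, with no new data and no effect on sample size or the primary analysis.
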